### Sample size

On the basis of previous study [12], it is calculated by Tukey-Kramer test that 220 participants will be required (55 in each group) to detect a difference of 50mmHg in the PaO_2_/FiO_2_ ratio between groups, assuming a standard deviation (SD) of 50mmHg in the control group (80% power, *α*= 0.05). If the follow-up rate is assumed to be 90%, 244 participants with 61 in each group will be needed. Sample size calculation was performed by PASS 11 software.

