### Design

Patients with diagnosed SCAP are randomized to the following four groups at a 1:1:1:1 ratio:Group 1 (control group): standard ICU patient care+100ml of normal saline once a day for 5 days. Standard ICU patient care involves ventilatory, hemodynamic, antimicrobial, nutritional, and other supports according to the guidelines for the diagnosis and treatment of community-acquired pneumonia in Chinese adults (2016 Edition). At present, there are no relevant guidelines to recommend methylprednisolone as a therapeutic drug for SCAP, which indicates that a consensus has not been reached and disputes still exist. Thus the placebo control group is still needed.Group 2: standard ICU patient care+40mg of methylprednisolone (dissolved in normal saline with a final volume of 100ml) once a day for 5 days.Group 3: standard ICU patient care+80mg of methylprednisolone (dissolved in normal saline with a final volume of 100ml) once a day for 5 days.Group 4: standard ICU patient care+120mg of methylprednisolone (dissolved in normal saline with a final volume of 100ml) once a day for 5 days.

Researchers will explain the research procedures in detail to the subject or agent to obtain the informed consent and will evaluate intervention adherence during each visit. If a scheduled visit is delayed or canceled, the research team will contact the subject immediately. No concomitant care or intervention is prohibited during the study. The trial is planned to be followed up for 28 days after randomization. The schedule of enrolment, interventions, and assessments is shown in Fig. 1.

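### With a common SD of 50 mmHg, the stated sample-size inputs give about 25 per group (32 to 34 for all-pairs power), not 55, so at least one input is mis-stated or undisclosed

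*Protocol article*

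**What the plan says.** The Sample size section of the protocol article states that "it is calculated by Tukey-Kramer test that 220 participants will be required (55 in each group) to detect a difference of 50mmHg". The outcome being sized is the primary one, oxygenation at day 5. For variability the section offers a single figure: "assuming a standard deviation (SD) of 50mmHg in the control group". The error rates appear as "80% power, *α*= 0.05". The software is named: "Sample size calculation was performed by PASS 11 software". The Design section gives four arms: "Patients with diagnosed SCAP are randomized to the following four groups at a 1:1:1:1 ratio". A cited earlier study is named as the basis.

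The section gives no SD for the three methylprednisolone arms and no pattern for the four means. It also does not say whether the 80% refers to one pair, any pair or all pairs.

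**The concern.** A difference of 50 mmHg against an SD of 50 mmHg is a standardised difference of 1.0, which is large. Four-group pairwise comparisons at that effect size do not usually need 55 per arm, even after adjustment for six pairs.

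This paragraph is the article's only justification for the trial's size, and it is likely to be carried into the final report. If SD 50 holds in every arm, the paragraph claims 80% power where the inputs give over 99%, and it overstates the difference that the trial is sized to detect. If a larger SD was used, the article misreports the variability that was planned for. In either case a reader cannot reconstruct why 55 was chosen.

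**Working it through.** **Inputs.** From the Sample size section: Tukey-Kramer, difference 50 mmHg, SD 50 mmHg (control group), power 80%, alpha 0.05. From the Design section: four groups of equal size. Assumption made here: the SD is 50 mmHg in all four arms.

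**Plan's own figure.** 4 × 55 = 220 is consistent as a sum. The step to check is from the inputs to 55.

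**Per-pair power.** With n per group:
- degrees of freedom: df = 4(n − 1)
- critical value: c = q(0.95; 4, df)/√2, where q is the studentised range quantile
- noncentrality: δ = 50/(50 × √(2/n)) = √(n/2)
- power: P(|T| > c), with T noncentral t on df with noncentrality δ

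| n per group | df | c | δ | Power |
|---|---|---|---|---|
| 24 | 92 | 2.617 | 3.464 | 79.9% |
| 25 | 96 | 2.615 | 3.536 | 81.9% |
| 55 | 216 | 2.589 | 5.244 | 99.6% |

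So 25 per group (100 in total) is the 80% answer, and 55 is 55/25 = 2.2 times that.

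**All-pairs power** (every truly different pair significant; simulated, pooled variance, SD 50):
- means 0/0/0/50 and 0/50/50/50: 80% is passed at n = 32
- means 0/0/50/50 and 0/50/100/150: 80% is passed at n = 34
- at n = 55, all four patterns give about 98.5% to 99%

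**Other adjustments, 80% power, same inputs:**
- any-pair Tukey with means 0/50/50/50: about 16
- unadjusted t comparison (LSD): 17
- overall F test with means 0/25/25/50: 23
- Bonferroni over six pairs, t-based: 26
- Scheffé: 28

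None of these reaches 55.

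**Working back from 55.** Per-pair power at n = 55 is 80% when the standardised difference is 0.655. This means one of two things:
- SD 50 kept: detectable difference = 0.655 × 50 ≈ 33 mmHg
- difference 50 kept: common SD = 50/0.655 ≈ 76 mmHg

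On the all-pairs definition, a common SD of about 64 to 66 mmHg gives 80% at 55, depending on the pattern of means.

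**Dropping the common-SD assumption.** With control SD 50 and n = 55, all-pairs power is about 80% when the active-arm SD is about 72.5 mmHg (means 0/50/50/50) or about 67.5 mmHg (means 0/50/100/150).

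**Interval-width criterion.** The Tukey half-width with SD 50 is q × 50/√n, which is 24.9 mmHg at n = 54 and 24.7 at n = 55. A target half-width of 25 mmHg (half of 50) thus needs 54 per group, with no use of the 80%. Requiring coverage and a half-width of at most 25 with probability 0.80 needs 59.

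**The case against.** The strongest reply is that the SD of 50 mmHg is stated for the control group only. The common SD is an assumption of this check. With larger active-arm SDs of roughly 67 to 73 mmHg and the all-pairs definition, every printed figure can be true together. The pattern of means matters too: with a common SD of 50 and means 0/50/50/85, all-pairs power at 55 is only about 76%, because some true differences are then 35 mmHg. A journal article may also leave per-arm SDs, assumed means and the type of power to the full protocol, and neither the cited study nor the software run is available here.

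Most of this stands, and it limits the conclusion. A reader might infer that either the stated power or the stated SD must be wrong. The documents do not support that: the difference, undisclosed active-arm SDs, the means or a width criterion could each account for 55. What does not stand is the idea that the paragraph is merely brief. It offers test, difference, SD, power and alpha as the basis for 55, and with the only SD it prints they do not lead there. Every explanation above needs an input that is absent or differs from what is printed. A width criterion would also contradict the stated aim of detecting a difference with 80% power.

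A reader might also infer that the trial is underpowered. The discrepancy runs the other way: 55 exceeds what the stated inputs require. Nor can one conclude that twice too many patients are being enrolled, since the true planning SD is unknown.

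**Conclusion.** The point holds as a failure of the stated inputs to yield the stated sample size. Assuming a common SD of 50 mmHg, they give about 25 per group on per-pair power. On all-pairs power they give 32 to 34, when each non-zero difference is at least 50 mmHg. The plan has 55, about 1.6 (55/34) to 2.2 times as many. At 55 evaluable per group, per-pair power for 50 mmHg is over 99%, and the difference detectable with 80% power is about 33 mmHg.

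At least one input is mis-stated or undisclosed, and the document does not allow one to say which. Adequacy of power on the stated inputs is not in question, and no analysis or decision rule changes. This is a defect of reporting and reproducibility that should be corrected; it does not threaten the trial's validity.

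**What to change.** Keep the enrolment. Retrieve or re-run the software calculation and restate the paragraph so that these agree: number per group, difference, SD in all four arms, assumed group means, and type of power (per pair, any pair or all pairs).

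- If SD 50 mmHg holds in all arms, state that 55 evaluable per group gives 80% per-pair power for about 33 mmHg, or over 99% for 50 mmHg.
- If a larger common SD was used (about 76 mmHg per pair, or 64 to 66 mmHg for all pairs), state it in place of 50.
- If the active arms were given larger SDs than control, print them.
- If the size came from an interval-width target, say so and remove the 80% power claim for 50 mmHg.

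The cost is one paragraph of rewording, with no additional patients and no change to the conduct of the trial.

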### Statistical analysis

We will show *n* (%) for categorical variables and median (interquartile range) for continuous variables with non-normal distribution or mean (SD) for those with normal distribution. Data for the primary and secondary outcome will be analyzed on intention-to-treat analysis, and missing data will be handled by multiple imputation method. If variances are equal, comparison of continuous variables will be evaluated by one-way analysis of variance, followed by the least significance difference procedure; otherwise, the Games-Howell procedure will be followed. The *χ*^2^ test followed by the Bonferroni method will be used to evaluate the comparison of categorical variables. Subgroup analysis will be used when appropriate. SPSS 18.0 software will be employed for statistical analysis. Significance level is set at 0.05.

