## Background

Community-acquired pneumonia (CAP) is a common clinical inflammatory disease, which is mainly caused by pathogenic microorganism infection. In Europe and North America, the annual incidence of adult CAP is 5–11 per thousand adult population and increases gradually with age [1]. Accounting for about 10–20% of hospitalized CAP, patients with severe CAP (SCAP) often need to be admitted to intensive care unit (ICU) for fluid resuscitation, necessary mechanical ventilation and other support treatment, and the 30 day mortality rate of these patients is as high as 23–47% [2–4]. Such a high mortality is not only related to the infection of SCAP itself, but also may be associated with the excessive inflammatory reaction after infection. The latter can cause extensive damage of alveolar epithelial cells and capillary endothelial cells, leading to the decrease of pulmonary surfactant, lung compliance, and lung consolidation, and eventually lead to the occurrence of acute respiratory distress syndrome.

From the perspective of pathological mechanism, the systemic inflammatory response produced by SCAP is the consequence of self-destruction caused by over activation of body defense mechanism, rather than the direct damage caused by pathogenic microorganism infection. Therefore, the treatment should not be limited to the control of infection and supportive treatment for respiration and circulation, but should find a way to block or reduce the self-destruction caused by the excessive inflammatory reaction and prevent tissue and cell damage.

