### Primary outcome

PaO_2_/FiO_2_ ratio at day 5 following randomization

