### Secondary outcomes

Twenty-eight-day mortality (death proportion within 28 days of randomization)Sixty-day mortality (death proportion within 60 days of randomization)Ventilator-free days at 28 days (the number of days free from mechanical ventilator support in the first 28 days following randomization)Mechanical ventilation duration at 28 days (the number of days during mechanical ventilation within 28 days of randomization).Endotracheal intubation rate (the proportion of patients requiring endotracheal intubation within 28 days of randomization)Time for temperature recovery (the number of days required for body temperature to return to normal)Duration of vasopressors use (the number of days required for continuous use of vasopressors)Serum CRP and interleukin-6 level at day 5 following randomizationHospital stayFrequency of nosocomial infections (the number of ventilator-associated pneumonia, blood stream infection or candidemia within 28 days of randomization)Gastrointestinal hemorrhage (the proportion of gastrointestinal bleeding patients requiring additional medication, blood transfusion, or surgical intervention within 28 days of randomization)Hyperglycemia (the proportion of patients with hyperglycemia requiring insulin injection within 28 days of randomization)

All adverse events and other unintended effects of trial interventions or trial conduct will be collected and documented, regardless of severity. Participants who suffer harm from these events will be compensated accordingly.

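### Multiple imputation of the day-5 PaO2/FiO2 ratio makes no exception for death, so as written patients who die before day 5 receive values modelled from survivors

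*Protocol article*

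**What the plan says.** Under Primary outcome the protocol article names one variable: "PaO_2_/FiO_2_ ratio at day 5 following randomization". Under Statistical analysis it fixes how absent values are handled: "Data for the primary and secondary outcome will be analyzed on intention-to-treat analysis, and missing data will be handled by multiple imputation method". Continuous variables are then compared by one-way analysis of variance with pairwise follow-up procedures.

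Death appears under Secondary outcomes, as mortality at 28 days ("Twenty-eight-day mortality (death proportion within 28 days of randomization") and at 60 days. Neither the primary outcome nor the imputation rule mentions it.

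The patients are in intensive care. Invasive ventilation and septic shock on vasopressors are qualifying criteria, and Background says of severe cases that "the 30 day mortality rate of these patients is as high as 23–47" per cent.

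**The concern.** A blood gas that was due on day 5 but not taken is a missing value. A day-5 ratio for a patient who has died does not exist. Multiple imputation is built for the first case: it fits a model to patients with a measurement, all of whom are alive at day 5, and predicts for the rest. Applied to the dead, it credits them with the oxygenation of survivors who have similar covariates.

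Early death in severe pneumonia is plausibly linked to poor gas exchange, so the error has a direction. An arm that loses more of its sickest patients early is flattered on the primary outcome, and an arm that keeps them alive is penalised. This matters for a dose comparison. Background allows that glucocorticoids may lower mortality and cites a study of higher doses with more superinfection, so unequal early deaths between arms are within the trial's own premise. The same rule reaches CRP and interleukin-6 at day 5.

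**Working it through.** The protocol gives no figure for day-5 deaths or for the effect of imputing them, so there is none to reproduce. Its sample-size figures serve only as a scale.

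**Inputs from the protocol**
- SD 50 mmHg, from Sample size: "assuming a standard deviation (SD) of 50mmHg in the control group".
- Target difference 50 mmHg, from the same section: "to detect a difference of 50mmHg in the PaO_2_/FiO_2_ ratio between groups".
- 55 per group, raised to 61 per group for 90% follow-up.
- 30-day mortality 23–47%, a literature figure in Background.

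**Assumed**
- The proportion dead by day 5 in each arm.
- How strongly early death is tied to low oxygenation.

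**Step 1. How many deaths by day 5?** With a constant hazard over 30 days, the proportion is 1 − (1 − m)^(5/30).
- m = 0.23: 1 − 0.77^(1/6) = 4.3%, or 0.043 × 61 ≈ 3 per arm.
- m = 0.47: 1 − 0.53^(1/6) = 10.0%, or 0.100 × 61 ≈ 6 per arm.
- If instead one third to one half of 30-day deaths fall by day 5, the range is 0.23/3 ≈ 8% to 0.47/2 ≈ 24%, or about 5 to 14 per arm.

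**Step 2. Upper bound on the bias.** Bias here is measured against the mean over all randomised patients, with each early death keeping a notional low day-5 value. Suppose that the proportion p who die are exactly those with the lowest values, and that there is no dose effect. The mean of the survivors is then too high by 50 × φ(z_p)/(1 − p), where z_p is the p-quantile of the standard normal distribution.

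| p | φ(z_p)/(1 − p) | Shift (mmHg) |
|---|---|---|
| 5% | 0.1086 | 5.43 |
| 10% | 0.1950 | 9.75 |
| 15% | 0.2743 | 13.72 |

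- 10% versus 5%: 9.75 − 5.43 = 4.3 mmHg in favour of the arm with more deaths.
- 15% versus 5%: 13.72 − 5.43 = 8.3 mmHg in favour of the arm with more deaths.
- Equal p: 0.

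**Step 3. What reduces it.** The formula is the survivors-only shift, that is, imputation with no useful covariates.
- If the correlation between oxygenation and death is 0.5, the shifts halve to 2.2 and 4.1 mmHg.
- A simulation of regression imputation on one baseline covariate, correlated 0.3–0.7 with the day-5 ratio, lowers them further.

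| Early deaths | Survivors-only shift, complete link to oxygenation | With covariate | Survivors-only shift, correlation 0.5 | With covariate |
|---|---|---|---|---|
| 10% vs 5% | 4.3 | about 2.7–4.1 | 2.2 | about 1.2–2.0 |
| 15% vs 5% | 8.3 | about 5.3–7.8 | 4.1 | about 2.3–3.9 |

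**Step 4. Scale.** The standard error of a pairwise difference at 55 per group is 50 × √(2/55) = 9.5 mmHg. The bounds are 4.3/9.5 = 0.45 and 8.3/9.5 = 0.87 of a standard error, and 4.3/50 = 9% and 8.3/50 = 17% of the target difference.

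**The case against.** The strongest reply is that the text never calls the dead missing. An article that gives its analysis in one paragraph may leave the handling of death to a fuller plan. The first half is right: that imputation covers the dead is an inference from a rule with no exception. But the rule is stated, not omitted. Intention to treat keeps the patient in, and imputation is the only route given to a value.

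The second reply is that the effect is modest and conditional, and this stands. The figures above are upper bounds under their assumptions, and below one standard error.

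Three stronger readings are tempting and are not supported:
- **That the dose comparison is biased by a known amount.** Day-5 deaths per arm are not in the protocol. Background's mortality is a 30-day literature figure, and the allowance under Sample size ("If the follow-up rate is assumed to be 90" per cent) says nothing about death.
- **That imputation can reverse the result.** In a simulation with no effect and early deaths of 10% in control and 20% in the treated arm, imputation gave +4.2 mmHg, while scoring each death as 50 mmHg gave −12.0. Most of that gap comes from the low value chosen for death. It is a change of estimand, not a bias of imputation.
- **That harm would be hidden from the trial.** Mortality at 28 and 60 days is a secondary outcome, all adverse events are recorded, and a monitoring committee reviews the data. Only the primary comparison is affected.

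**Conclusion.** The point holds as a defect in a stated rule. Followed as written, the plan gives patients who die before day 5 a ratio drawn from a model of survivors, and where early deaths differ this favours the arm with more of them. The direction rests on early death being linked to poor oxygenation. The size rests on assumed death rates, for which the protocol gives no figures.

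It should be fixed, but it is not a fatal flaw. A reader might infer that the primary mean comparison must be replaced by a rank test. The protocol does not force that: such a test would change the estimand and would no longer match a sample size built on a 50 mmHg mean difference. It is better placed beside the mean comparison.

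**What to change.** In Statistical analysis, before unblinding:

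1. Limit multiple imputation to patients alive at day 5 who have no blood gas. Apply the same limit to day-5 CRP and interleukin-6.
2. State that the mmHg comparison is among patients alive at day 5, and report it with day-5 mortality by arm.
3. Add a prespecified analysis of all randomised patients that ranks death before day 5 below the lowest observed ratio, using a Kruskal-Wallis test with multiplicity-adjusted pairwise rank tests. Require any dose claim to be consistent with it.

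Step 2 does not remove selection by survival: a survivor comparison carries the full shift shown in the working. It makes the comparison explicit, and steps 2 and 3 show the deaths beside it.

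The cost is one extra analysis and a narrower meaning for the mmHg difference, which becomes a survivor estimate. The analysis of variance and the sample-size basis can stay. Recruitment is under way, so the change should be dated and recorded as made blind to outcome by arm.

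### The day-5 PaO2/FiO2 analysis leaves out the baseline value of the same measure: it is valid, but expected to lose precision where doses differ by less than 50 mmHg

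*Protocol article*

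**What the plan says.** The Primary outcome section defines a single raw value: "PaO_2_/FiO_2_ ratio at day 5 following randomization". It is not a change from baseline.

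The Statistical analysis section sets one rule for continuous variables: "If variances are equal, comparison of continuous variables will be evaluated by one-way analysis of variance". For the pairwise step, and for the case of unequal variances, that sentence goes on: "followed by the least significance difference procedure; otherwise, the Games-Howell procedure will be followed". The primary outcome falls under this rule because no other method is named for it. In both branches treatment group is the only explanatory factor. The article mentions no ANCOVA, change score or other baseline adjustment, and the Randomization section describes no stratification by oxygenation.

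The Participants section lists a PaO2/FiO2 threshold among the minor criteria for severe pneumonia. A patient can also qualify on one major criterion alone (invasive ventilation, or septic shock needing vasopressors).

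The Sample size section plans "to detect a difference of 50mmHg in the PaO_2_/FiO_2_ ratio between groups". Its statement on spread is "assuming a standard deviation (SD) of 50mmHg in the control group", and its error rates are given as "80% power, *α*= 0.05".

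**The concern.** The eligibility rules put no upper limit on PaO2/FiO2 at entry: the threshold is one minor criterion among six, and a major criterion suffices without it. Patients may therefore start from very different levels of oxygenation. If the starting level predicts the day-5 level, a one-way ANOVA leaves that predictable part in the error term. An analysis that conditions on baseline would remove it.

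The trial asks whether efficacy depends on dose, with arms at 40, 80 and 120 mg and a placebo arm. If neighbouring doses differ by less than the 50 mmHg used for sizing, the width of the interval decides whether they can be told apart. Baseline adjustment is a cheap way to narrow it.

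This is not a gap that an analysis plan would simply fill. The article names a method that cannot carry a covariate, so an analysis plan using ANCOVA would have to depart from it.

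**Working it through.** **Inputs.**
- From the Sample size section: difference 50 mmHg, SD 50 mmHg (stated for the control group, taken here as common to all arms), power 80%, alpha 0.05 (taken as two-sided), 55 per group before loss.
- Assumed, because the document gives no value: correlation r between baseline and day-5 PaO2/FiO2 of 0.3, 0.5 or 0.7.
- Illustrative: a dose-to-dose difference of 25 mmHg, half the design target. The document states no expected difference between doses.

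**The plan's own figure.** The article states "220 participants will be required (55 in each group") by the Tukey-Kramer test. The stated inputs do not lead to 55:
- one Tukey comparison of 50 mmHg needs 25 per group;
- all Tukey pairs need 32 to 34 per group when every non-zero difference is at least 50 mmHg;
- a plain two-sample comparison needs 16 per group.

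The loss step agrees within rounding: 220 / 0.9 = 244.4, against 244 stated. The mismatch at 55 is a separate matter, and nothing below depends on it. At 55 per group a single Tukey comparison of 50 mmHg has 99.6% power.

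**Unadjusted precision.** SE of a pairwise difference = SD × √(2/n) = 50 × √(2/55) = 9.53 mmHg.

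**Adjusted precision.** With baseline as a linear covariate, residual variance = SD² × (1 − r²), so the SE = 9.53 × √(1 − r²). The single degree of freedom spent on the slope is ignored; the unadjusted error term has 4 × 54 = 216.

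- Difference detectable with 80% power, unadjusted for multiplicity (LSD) = (1.96 + 0.84) × SE.
- Power for 25 mmHg under LSD (normal approximation) = Φ(25/SE − 1.96).
- n for equal precision = 55 × (1 − r²).

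| r (assumed) | 1 − r² | SE, mmHg | Detectable difference, mmHg | Power for 25 mmHg, LSD | Power for 25 mmHg, one Tukey pair | n per group for the precision of 55 unadjusted |
|---|---|---|---|---|---|---|
| 0 (no gain) | 1.00 | 9.53 | 26.7 | 74.6% | 51.4% | 55 |
| 0.3 | 0.91 | 9.10 | 25.5 | 78.5% | 56.4% | 50 |
| 0.5 | 0.75 | 8.26 | 23.1 | 85.7% | 66.9% | 41 |
| 0.7 | 0.51 | 6.81 | 19.1 | 95.7% | 85.9% | 28 |

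The gain is modest at r = 0.3 and substantial at r = 0.7.

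**The case against.** The strongest reply is that nothing here is an error. In a randomised trial the unadjusted comparison is unbiased on average and keeps its type I error. That stands, and it rules out three stronger readings.

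*That chance baseline imbalance distorts the result.* If the baseline SD is also taken as 50 mmHg (an assumption; the article gives 50 only for its sample-size calculation), a baseline difference between two arms of 55 has an SE of 9.5 mmHg. A two-SE imbalance carried over at a slope of 0.5 moves that comparison by about 10 mmHg (2 × 9.5 × 0.5). This is ordinary sampling error, already counted in the ANOVA standard error and in the reported interval. It is not an added bias.

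*That the trial is underpowered without adjustment.* At the article's own difference and SD, 55 per group gives far more than 80% power for one comparison. The loss bears only on differences below 50 mmHg, and the article does not say how large dose-to-dose differences are expected to be.

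*That adjustment is sure to narrow every interval.* Broad eligibility shows that baseline may vary. It does not show that baseline predicts day 5 after five days of intensive care and trial drug. The correlation is unknown, and at 0.3 the SE falls only from 9.53 to 9.10 mmHg.

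Two further cautions stand. A baseline PaO2/FiO2 for every patient is inferred: those qualifying on a major criterion do not need one for eligibility, and the schedule figure is not shown. No baseline CRP or interleukin-6 is mentioned.

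The reply that covariates belong in an unseen analysis plan carries less weight, because the article has already committed to a method without one.

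**Conclusion.** The point holds as one of efficiency. The article commits the primary outcome to procedures that ignore baseline PaO2/FiO2, and an adjusted analysis is expected to be more precise at almost no cost. For an assumed correlation of 0.3 to 0.7, the residual variance falls by 9% to 49% and the SE of a pairwise difference by about 0.4 to 2.7 mmHg (9.53 − 9.10 and 9.53 − 6.81). This rests on a common SD of 50 mmHg, 55 analysed per group, a linear relation and a baseline value for every patient. The direction of the effect is well founded; its size is uncertain because the correlation is not given. It is worth changing because the trial sets out to separate doses, but the planned analysis would not be invalid without the change.

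**What to change.** State, before unblinding, that the primary analysis is an ANCOVA of day-5 PaO2/FiO2 on treatment group with baseline PaO2/FiO2 as covariate. To replace the present Games-Howell branch, specify heteroscedasticity-robust standard errors if variances differ. Keep the unadjusted ANOVA as a sensitivity analysis. Fixing this in advance also prevents a later choice between adjusted and unadjusted results.

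Record the pre-randomisation PaO2/FiO2 for every patient, including those who qualify on a major criterion alone. Apply the same model to CRP and interleukin-6 only if a baseline value is collected.

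The cost is a short amendment to the analysis text and no extra patients. If the entry blood gas is already on the case report form for everyone, no new data are needed. If not, one field must be added and, since recruitment has begun, values for patients already enrolled must be taken from their records where available. How the pairwise comparisons are corrected for multiplicity is a separate question that this change does not settle.

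### A variance check decides whether the primary dose comparisons are multiplicity-adjusted, and multiple imputation leaves that check without a single answer unless it is made once

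*Protocol article*

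**What the plan says.** The primary outcome is the PaO2/FiO2 "ratio at day 5 following randomization" (Primary outcome), which is continuous. Three statements in the Statistical analysis section then apply to it:

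- Missing data, for primary and secondary outcomes alike: "missing data will be handled by multiple imputation method".
- First branch: "If variances are equal, comparison of continuous variables will be evaluated by one-way analysis of variance", with LSD as the follow-up procedure.
- Second branch: "otherwise, the Games-Howell procedure will be followed".

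The same section adds "Significance level is set at 0.05". It names no variance test or cut-off, and does not say whether variances are judged once or in each imputed dataset. The Sample size section assumes 90% follow-up, so about 10% missing data is planned for.

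**The concern.** The two branches differ in more than their variance assumption. LSD tests each pair at the unadjusted level once the ANOVA is significant. Games-Howell holds the error rate across all six pairs. A preliminary look at the variances therefore settles the multiplicity standard of the trial's main result, although the spread of the data has no bearing on how strictly six dose comparisons should be judged.

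Multiple imputation adds a second problem. It produces several completed versions of the trial, and whether variances are equal can be true in some and false in others. Read literally, the rule can then call for LSD and Games-Howell within one trial. Someone has to choose with the data in hand, and the choice can change which doses are declared different.

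**Working it through.** **Inputs from the protocol.** Four arms at 1:1:1:1; SD 50 mmHg (stated for control only); a planned difference of 50 mmHg; alpha 0.05 (two-sided assumed); 55 evaluable and 61 enrolled per arm. The protocol gives no figure on this point to reproduce. Its attrition step confirms the missing-data rate: 220/0.9 = 244.4, against 244 stated.

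**Inputs assumed.** Levene's test at 0.05, 5 or 20 imputations, normal outcomes, data missing at random, and the SDs of the active arms.

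**Step 1. How far apart are the branches?** With SD 50 and 61 per arm, the standard error of a pairwise difference is 50 × √(2/61) = 9.05 mmHg.

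- LSD, pairwise step: 1.97 × 9.05 = 17.8 mmHg.
- Games-Howell: 2.59 × 9.05 = 23.4 mmHg (23.6 with pairwise degrees of freedom).

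LSD also needs a significant ANOVA, with F above 2.64. With F = 61 × S/(3 × 50²), where S is the sum of squared deviations of the four arm means, the largest difference must reach:

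- 18.0 mmHg if the means split two against two;
- 20.8 mmHg if they split one against three;
- 25.5 mmHg if two arms lie midway between the extremes.

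The ANOVA gate therefore narrows the gap between branches, and in the last pattern reverses it for the largest pair. When several doses differ, the gate is open and the smaller pairwise differences are judged at 17.8 in one branch and 23.4 in the other.

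**Step 2. How often do imputed copies disagree on the check?** Share of simulated trials in which at least one copy differs from the others (61 per arm, 10% missing, regression imputation by arm with an assumed baseline correlation of 0.5, 1,500 trials per row):

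| True SDs | 5 imputations | 20 imputations |
|---|---|---|
| 50/50/50/50 | 14% | 23% |
| 50/55/60/60 | 25% | 40% |
| 50/50/60/70 | 26% | 41% |
| 50/60/70/80 | 19% | 30% |

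A simpler within-arm normal imputation without a covariate, with 20 imputations, gave 19–27% for equal SDs and 42–50% for 50/50/60/60 across repeated runs. Together the ranges are about 14–27% (equal) and 19–50% (unequal).

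**Step 3. How often does it matter?** Share of trials in which the copies split and the two branches also disagree on at least one pair (20 imputations, 10% missing, LSD only after a significant ANOVA, each branch's conclusion taken from the majority of copies):

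| Assumed means (mmHg) | Equal SDs, or 50/50/60/60 |
|---|---|
| 0/0/0/0 | about 1–4% |
| 0/20/20/20 | 9%, 19% |
| 0/10/20/30 | 13%, 26% |
| 0/15/30/50 | about 17%, up to 29% |

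For 0/15/30/50 the branches disagreed on some pair in about 62% of trials, whether or not the copies split.

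**Step 4. Does a fixed analysis work?** Pooling a pairwise difference with an unequal-variance standard error by Rubin's rules gave simulated type I error of 0.039–0.060 over 16 settings of SD, missingness and number of imputations. Simulation error is √(0.05 × 0.95/1500) = 0.006, so this is compatible with the nominal 0.05.

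**The case against.** The strongest reply is that nothing in the protocol requires the variance check in each imputed dataset. One check on the observed data gives one branch for all copies, and the timing, the test and the pooling rule are details that an article leaves to an analysis plan. That is correct, and their absence is not the point here. But a single check removes only the disagreement between copies. It still leaves the data to choose between an unadjusted and an adjusted comparison, and step 3 shows that this choice often matters when doses differ by degrees.

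A second reply is that the practical effect is small. A split counts even if one copy in 20 differs. On the question of whether any pair at all is significant, a split with a changed answer occurred in about 1% of trials under the null, 0% when every active arm differs from control by 50 mmHg, 0.3% with means 0/20/35/50 and 1.5–3.0% with a 15 mmHg effect. This stands: the overall answer is rarely at risk. The trial, however, asks which dose is best. The figures for individual pairs in that check were 1.5–10%, and 32% with the graded means.

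Three stronger readings are tempting, and the documents do not support them:

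- A reader might infer that these procedures cannot be combined after imputation. They can. LSD and Games-Howell both rest on mean differences with standard errors, which Rubin's rules pool, and F and chi-square statistics have their own combination rules. Only the Games-Howell studentized-range p-value lacks a direct standard pooled form.
- A reader might count the chi-square tests as part of the primary analysis. The protocol reserves them for categorical variables.
- A reader might infer that any difference between 17.8 and 23.4 mmHg flips with the branch, or that the trial will fall back on one imputed dataset. The ANOVA gate rules out the first as a general statement, and the protocol plans multiple imputation.

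**Conclusion.** The point holds in limited form. The protocol positively states a rule under which an unspecified variance check decides whether the primary dose comparisons carry a multiplicity adjustment, and imputation makes the rule ambiguous unless the check is made once. At the protocol's own 10% loss the ambiguity is common (roughly 14–50% of trials across the settings tried). It changes a pairwise conclusion mainly when true dose effects are graded (roughly 17–29% for 0/15/30/50), and seldom under the null (about 1–4%). These rates rest on the assumed test, number of imputations, imputation model, arm SDs and means; the protocol supplies only the control SD, the arm size and the loss rate. The change should be made before unblinding, but the point does not show the planned analysis to be invalid.

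**What to change.** Remove the variance check for the primary outcome and fix one analysis: a linear model with arm as a factor and heteroscedasticity-robust (unequal-variance) standard errors. Estimate the arm contrasts in each imputed dataset, pool estimates and standard errors by Rubin's rules, and apply one named multiplicity adjustment to the pooled contrasts whatever the variances. A method that needs only the pooled p-values, such as Holm, avoids the studentized-range difficulty. Skewed secondary outcomes, such as ventilator-free days or hospital stay, need not be forced into this model.

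The cost is a rewording of the analysis sentences. If variances are in fact equal, the loss of precision is negligible: with the Games-Howell criterion as a guide, the bar moves from 23.4 to 23.6 mmHg. The real price is a higher bar for a single pair than unadjusted LSD sets. The sample size need not rise on this account: it was planned with Tukey-Kramer, itself an adjusted procedure, whose simulated power for one 50 mmHg pair at 55 per arm and SD 50 is about 99.6%.
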